### Data management and statistical analysis

All study data will be collected and managed using Research Electronic Data Capture (REDCap) [30], a secure web-based application. Research assistants will use tablets with online access to the REDCap database for direct data entry and informed consent procedures.

For the primary objective evaluating the impact of the comfort menu and cart on the experience of older patients we will use the questionnaire adapted from Lichen et al. (2021) and McCusker et al. (2018). For the secondary objectives evaluating the impact of a comfort menu and cart on the experience of medical and multidisciplinary staff involved in caring for older patients treated in the ED, we will use the the questionnaire adapted from Lichen et al. (2021).

Data analysis will be performed using Stata version 17 (StataCorp, College Station, TX). All statistical tests will be two-tailed with an alpha error of 0.05. Numerical variables will be reported as means and standard deviations or medians and interquartile ranges (IQR) depending on their distribution, which will be assessed visually and using the D’Agostino-Pearson test for normality. Categorical variables will be described as absolute counts and proportions. Numerical variables will be compared using Student’s t-test or ANOVA for normal distributions and Wilcoxon or Kruskal-Wallis tests for non-normal distributions. As appropriate, categorical variables will be compared using the chi-square test or Fisher’s exact test. Analyses will be adjusted to account for potential confounding variables, such as baseline frailty, cognitive impairment, and clinical severity. Missing data will be handled though mixed effects model.

All relevant data from this study will be made available upon study completion.

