## Methods

### Study design

This study will utilize a quasi-experimental, before-and-after design [7]. Schedule of enrolment, assessments and intervention is summarized in Fig 1.

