#### Sample size calculation.

The sample size calculation was based on the study by Lichen et al. (2021), which reported a difference of 0.98 on a Likert scale (ranging from 1 to 6) when assessing patient experience before and after the comfort cart intervention [3]. Considering a power of 90% and a significance level of 5%, 132 patients will be required in each group (pre- and post-intervention), totaling 264 participants.

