### Data collection

#### Recruitment.

A trained research assistant will recruit participants in the ED, working 25 hours per week (five 5-hour shifts between 10:00 am and 10:00 pm) over six months (three months pre-intervention, from April 2026 to June 2026, and three months post-intervention, from July 2026 to September 2026). The assistant will conduct active searches for potential participants. Eligible patients will be invited to provide informed consent.

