**Table pone.0332773.t002:** 

Demographics	Full name, medical record number, ED visit number, date of birth, postal code, sex, date and time of ED admission
**Source of information**	If not the patient, the source’s full name, date of birth, sex, and relationship to the patient will be recorded
**Sensory deficits**	Presence and type of visual and/or hearing impairments
**History of falls**	Number of falls in the past year, circumstances surrounding the falls
**Comorbidity**	Assessed using the Charlson Comorbidity Index (CCI) [12–15]
**Risk of falls**	Assessed using the Memorial Emergency Department Fall Risk Assessment Tool (MEDFRAT) and the Carpenter instrument [16,17]
**Frailty**	Assessed using the Clinical Frailty Scale (CFS) version 2.0 [18,19]
**Clinical severity**	Assessed using the National Early Warning Score (NEWS) 2 [20,21]
**Mood**	Assessed using the 15-item Geriatric Depression Scale (GDS-15) [22]
**Geriatric vulnerability**	Assessed using the PRO-AGE Score [10]
**Acute mental status change (delirium)**	Assessed using the Delirium Triage Screen (DTS) and Brief Confusion Assessment Method (bCAM) [23]
**Quality of life**	Assessed using the Euro Quality of Life Instrument – 5D (EQ-5D) [24]
**Functionality**	Assessed using the Katz Index, Barthel Index, and Lawton Scale [25–27]
**Cognitive performance**	Assessed using the 10-Point Cognitive Screener (10-CS) [28]

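### The named patient-level tests ignore week-to-week variation although the cart is switched on once for the whole ED, so the 5% level is exceeded if comfort ratings correlate within weeks

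*Protocol article*

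**What the plan says.** Under Study design: "This study will utilize a quasi-experimental, before-and-after design". The Recruitment section places pre-intervention enrolment in April to June 2026 and post-intervention enrolment in July to September 2026, with one research assistant "working 25 hours per week (five 5-hour shifts between 10:00 am and 10:00 pm) over six months". Under Intervention, the cart is introduced for the whole department once the pre-intervention phase has ended.

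Under Data management and statistical analysis: "Numerical variables will be compared using Student’s t-test or ANOVA for normal distributions and Wilcoxon or Kruskal-Wallis tests for non-normal distributions". Categorical outcomes get chi-square or Fisher tests, and all tests are two-sided at 0.05. The same section promises adjustment for confounders, with frailty, cognitive impairment and clinical severity as examples. It names a mixed effects model for missing data only. No week, shift or calendar term appears.

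Under Sample size calculation, the planning study "reported a difference of 0.98 on a Likert scale (ranging from 1 to 6"), and then: "Considering a power of 90% and a significance level of 5%, 132 patients will be required in each group". No standard deviation, within-week correlation or design effect is given. The baseline data table includes "date and time of ED admission".

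**The concern.** No patient in a given recruitment week could have been in the other phase, so phase is a property of the week and not of the patient. Patients seen in the same week share crowding, staffing and room availability, all of which can plausibly move a comfort rating. Variation between weeks is then part of the error of the phase contrast, and the named tests leave it out.

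The direction follows from the design: any positive within-week correlation makes the standard error too small, the interval too narrow and the p-value too low. A few unusually busy or quiet weeks could then produce a nominally significant cart effect on the primary outcome. This concerns random variation within each phase. It is separate from a fixed difference between the two quarters, and from repeated interviews of the same staff.

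**Working it through.** **Inputs from the document.** 132 patients per phase, two-sided 5%, 90% power and a difference of 0.98 points on a 1 to 6 scale (Sample size calculation). Three months per phase and five shifts per week (Recruitment). April to June has 91 days and July to September 92, so about 13 weeks and 13 × 5 = 65 shifts per phase.

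**Assumed.** The intraclass correlation (ICC) within weeks, ranged over 0.01 to 0.05. The standard deviation (SD), which matters only for power.

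**The plan's own figure.** 132 per group cannot be reproduced directly because no SD is stated. Solving backwards, SD = 0.98 × √(132/2) / (1.960 + 1.282) = 2.46, a standardised difference of 0.98/2.46 = 0.40. The largest possible SD on a 1 to 6 scale is 2.5.

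**Size of the named tests, clustering by week.** Patients per week: m = 132/13 = 10.15. Design effect: DE = 1 + (m − 1) × ICC. The standard error should be larger by √DE, so the true two-sided size of a nominal 5% test is 2 × [1 − Φ(1.96/√DE)].

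| Weekly ICC | DE | √DE | True size |
|---|---|---|---|
| 0.01 | 1.09 | 1.04 | 6.1% |
| 0.02 | 1.18 | 1.09 | 7.2% |
| 0.05 | 1.46 | 1.21 | 10.5% |

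Simulated t-tests (13 weeks per phase, 10,000 runs, weeks independent of each other) rejected in 5.6%, 6.7% and 10.1% of runs. A separate simulation on a rounded 1 to 6 scale gave 7.6% at ICC 0.02 and 10.9% at 0.05.

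**Neighbouring weeks alike.** With an assumed week-to-week autocorrelation of 0.6, the t-test rejected in 8.6%, 12.2% and 21.6% of runs at ICC 0.01, 0.02 and 0.05.

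**Clustering by shift alone.** m = 132/65 = 2.03. At ICC 0.01, 0.05 and 0.10 the DE is 1.01, 1.05 and 1.10, and the true size 5.1%, 5.6% and 6.2%.

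**Does a week-level analysis restore the level?** With independent weeks, a comparison of weekly means rejected in 5.1 to 5.3% of simulated trials. With autocorrelation 0.6 it rejected in 7.4%, 9.7% and 14.1% at ICC 0.01, 0.02 and 0.05: better than the t-test, but not 5%.

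**Power with a correct standard error.** Power = Φ(0.98 / (SD × √(2 × DE/132)) − 1.96).

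| Weekly ICC | SD 1.5 | SD 2.0 | SD 2.46 (implied) |
|---|---|---|---|
| 0.01 | 99.9% | 97% | 87% |
| 0.02 | 99.8% | 96% | 85% |
| 0.05 | 99.3% | 91% | 77% |

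**The case against.** **The correlation is assumed.** Nothing in the document gives a within-week correlation or shows that one exists. At ICC 0 the tests are correct, and at 0.01 with independent weeks the error is about 6%. This stands, so the point must be worded conditionally.

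**The week is a chosen unit.** Crowding and staff on duty act mainly by shift or day, and clustering by shift alone gives only about 5 to 6%. This also stands and sets the lower end of the range. It does not argue against a week-level analysis, because shifts are nested in weeks and clustering by week covers correlation within shifts too.

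**The named tests are not the whole analysis, and a condensed article may leave error structure to an analysis plan.** It is true that adjustment and a mixed effects model are mentioned. But the covariates given as examples are patient-level, and the model is tied to missing data with no grouping factor. What the article does state is a set of independent-observation tests, and that choice does not fit a single switch in time.

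**Power.** A reader might infer that the stated 90% power also fails. The document does not support that. Power falls to about 87 to 77% only at the nearly maximal SD of 2.46 implied by 132 per group. At an SD of 2.0 or less it stays at 90% or more even at ICC 0.05. The missing SD is a separate question.

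**The fix has limits.** A week effect only partly corrects slow drift and cannot remove a shift common to a whole phase. The Discussion concedes that the design is weaker than a randomized trial for causality, but says nothing about correlated errors.

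**Conclusion.** The point holds in conditional form. The design makes exposure vary only between weeks, and the stated tests assume independent patients. If comfort ratings correlate within weeks, the phase standard error is too small. Under an assumed weekly ICC of 0.01 to 0.05, the true two-sided error is about 6% to 10 or 11% with independent weeks, more if weeks are autocorrelated, and about 5 to 6% if correlation is confined to shifts. The direction is certain for any positive correlation. The size rests on an ICC that the document does not give, and it does not depend on the SD. No conclusion about the 90% power follows. The change is worth making before recruitment because it is cheap and a single-switch design has no other safeguard against a run of unusual weeks.

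**What to change.** Replace the unclustered phase comparison, for the comfort item and the other patient outcomes, with a model that contains phase and the planned covariates. It should have either a random intercept for recruitment week or standard errors clustered by week with a small-sample correction (26 weeks, so about 24 degrees of freedom). Build week from the recorded admission date, counting from the first day of each phase so that no week spans both. The t, Wilcoxon and chi-square tests can remain as descriptive comparisons.

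State in the analysis section and the limitations that this covers short-term variation between weeks and within shifts, and that it does not remove slow drift or a difference common to a whole phase.

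The cost is analysis wording, with no new data. If the ICC is in fact zero, intervals are up to about 5% wider (t with 24 degrees of freedom 2.06 against 1.96; 2.06/1.96 = 1.05).

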**Table pone.0332773.t004:** 

ED readmissions	Number of ED visits since the initial visit
**Falls**	Number of falls since the initial visit
**Delirium incidence**	Assessed using the Family Confusion Assessment Method (FAM-CAM) [29] administered to a family member or caregiver
**Mood**	Assessed using the GDS-15
**Quality of life**	Assessed using the EQ-5D
**Functionality**	Assessed using the Katz Index, Barthel Index, and Lawton Scale
**Cognitive performance**	Assessed using the 10-CS
**Mortality**	If the patient has passed away, the date and cause of death will be recorded

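### The named adjustment examples leave out the ED-interview value of quality of life, function and mood, although each is collected and compared again at day 30 in a non-randomised design

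*Protocol article*

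**What the plan says.** Under Study design the protocol article states: "This study will utilize a quasi-experimental, before-and-after design". The two phases enrol different patients in consecutive quarters, April to June and July to September 2026 (Recruitment).

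The data table under Initial interview lists GDS-15 for mood, EQ-5D for quality of life, Katz, Barthel and Lawton for function, and 10-CS for cognition. The table under Follow-up interview repeats all of them at 30 days (± 2 days); for function it reads "Assessed using the Katz Index, Barthel Index, and Lawton Scale".

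Data management and statistical analysis names the tests: "Numerical variables will be compared using Student’s t-test or ANOVA for normal distributions and Wilcoxon or Kruskal-Wallis tests for non-normal distributions". It then commits to adjustment: "Analyses will be adjusted to account for potential confounding variables, such as baseline frailty, cognitive impairment, and clinical severity". A mixed effects model is given as the way to handle missing data, with no outcome structure, time term or phase contrast described.

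The second of the Secondary objectives labels these outcomes exploratory. Mood is not named there, in the Abstract or in Expected results; it appears only in the two data tables.

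**The concern.** Patients in the two phases are not randomised, so the phases may differ at the ED visit in function, quality of life or mood. A day-30 score carries part of that difference forward. If the comparison does not condition on where each patient started, the carried-over part is read as a 30-day benefit or harm of the cart.

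The outcome's own starting value is usually the best single guard against this, and here it is already in the database. The examples given are frailty, cognitive impairment and clinical severity. Frailty may partly stand in for function, but it is a weaker proxy for mood and quality of life. Leaving the starting value out also discards precision that the second measurement of each patient has made available.

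The Discussion presents the longitudinal 30-day view as a main contribution of the study, so these results are likely to be read with some weight despite their exploratory label.

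**Working it through.** **Inputs from the protocol article.** Size: "Considering a power of 90% and a significance level of 5%, 132 patients will be required in each group" (Sample size calculation). Tests: "All statistical tests will be two-tailed with an alpha error of 0.05" (Data management and statistical analysis).

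**Assumptions, because the document gives no figure.** Correlation rho between ED-interview and day-30 value: 0.3 to 0.7. Initial phase difference g: 0.1 to 0.3 SD. Correlation q of frailty with the ED-interview value: 0.5 to 0.8. Day-30 effect for the power comparison: 0.35 SD. Scores are in SD units and treated as roughly normal.

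**The plan's own figure.** The 132 per group is for the experience item (difference 0.98), not for the day-30 outcomes. No SD is stated, so it cannot be reproduced from the text; solving backwards gives SD = 0.98 × √(132/2) / (1.960 + 1.282) ≈ 2.46. That is a separate matter. Here 132 serves only as the number per phase.

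**Step 1: unadjusted day-30 comparison, no cart effect.** Expected spurious difference = rho × g. SE = √(2/132) = 0.1231. Rejection = P(|Z + rho·g/SE| > 1.96).

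| g (SD) | rho 0.3 | rho 0.5 | rho 0.7 |
|---|---|---|---|
| 0.1 | 5.7% | 6.9% | 8.8% |
| 0.2 | 7.8% | 12.8% | 20.6% |
| 0.3 | 11.3% | 23.0% | 40.0% |

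For example, at g = 0.2 and rho = 0.5 the spurious difference is 0.10 SD, and 0.10/0.1231 = 0.81 standard errors.

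**Step 2: adjustment for frailty only.** If frailty reflects the outcome's starting value with correlation q, the remaining bias is rho·g·(1 − q²) and the residual variance is 1 − rho²q². At rho = 0.5 and g = 0.2:

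- q = 0.5: bias 0.075, SE 0.1192, ratio 0.63, rejection 9.6% (9.5% by simulation, 4,000 trials)
- q = 0.7: bias 0.051, SE 0.1153, ratio 0.44, rejection 7.3%
- q = 0.8: bias 0.036, SE 0.1128, ratio 0.32, rejection 6.2%

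At the unfavourable end (rho 0.7, g 0.3, q 0.5) simulation gives 27.2%. At g = 0.1 and rho = 0.5 the rate is 5.3% to 6.1% over the same range of q, so little is then at stake.

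**Step 3: add the outcome's own ED-interview value.** Under this model the carried-over bias is removed. Simulated rejection is 4.8% to 5.3%.

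**Step 4: power for a 0.35 SD effect.** Noncentral t, 132 per phase. Residual variance is 1 unadjusted, 1 − rho²q² = 0.9375 with frailty only (rho = q = 0.5), and 1 − rho² with the own value:

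- Unadjusted: 81%
- Frailty only: 83%
- Own value: 84% at rho 0.3, 90% at rho 0.5, 98% at rho 0.7

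With an assumed 15% loss (132 × 0.85 ≈ 112 per phase), power is 74% unadjusted against 85% with the own value at rho 0.5.

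**Step 5: price of adjusting.** In the post phase the same interview asks about cart use before the scales are collected, so the ED-interview value may follow exposure. If the cart has already shifted it by s SD, adjustment removes rho × s from the estimated effect. For example, s = 0.2 (assumed) and rho = 0.5 removes 0.5 × 0.2 = 0.10 SD.

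**The case against.** The strongest reply is that the text excludes nothing. The covariates are offered as examples, the commitment to adjust is firm, and outcome-by-outcome covariates for exploratory endpoints are commonly left to an analysis plan. Much of this stands: own-value adjustment is compatible with the wording, and no contradiction is alleged. What remains is that the article does choose examples, gives confounding as the reason, and passes over the most obvious candidate among the variables it collects. An open list also lets the choice be made outcome by outcome once the data are seen.

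The unadjusted figures also describe an analysis that the plan does not end with. This stands. Step 2 is the closer comparison, and even it omits cognition and severity, which would absorb some more. Nothing in the document supports an initial difference of 0.2 to 0.3 SD in particular; consecutive quarters in one department with the same criteria might differ by less.

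Three stronger readings are tempting and not supported:

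- A reader might infer that independent-group tests are themselves wrong because patients are measured twice. The phases contain different people, so such tests are the correct type for the phase contrast; paired tests would answer another question.
- A reader might infer that no outcome has its starting value considered. Cognitive impairment is named and 10-CS is the ED cognitive screen, so cognition is at least partly covered.
- A reader might infer that the plan compares raw day-30 values only, or that the mixed effects model would count the initial difference as a cart effect. The text does not say whether values or changes are compared and gives the model no structure, so it neither proves the fault nor repairs it.

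Post-exposure measurement is a real risk of the remedy. It applies to mood as well, since the cart and menu include distraction items and conversation with a chaplain or social worker.

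**Conclusion.** The point holds in a limited form. For EQ-5D, Katz, Barthel, Lawton and GDS-15, a measured and probably strong confounder and predictor is absent from the named adjustment examples in a non-randomised comparison.

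The realistic size, given that some adjustment is promised, is the gap between frailty-only and own-value adjustment: about 7% to 9.6% against about 5% false rejections at rho 0.5, a 0.2 SD initial difference and q of 0.7 down to 0.5, and 83% against 90% power at q = 0.5. The 6% to 40% range is an upper bound for analyses left unadjusted. All of this rests on assumed correlations and initial differences. With a small initial difference the bias is negligible, and with rho 0.3 the power gain over the unadjusted test is only from 81% to 84%.

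The affected outcomes are exploratory. The primary experience outcome is not measured at an earlier time and is unaffected. The change is worth making because it is nearly free, not because the trial's main conclusion is at risk.

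**What to change.** In Data management and statistical analysis, add that day-30 EQ-5D, Katz, Barthel, Lawton, GDS-15 and 10-CS will each be regressed on phase, the same instrument's ED-interview value, and frailty, cognitive impairment and clinical severity, with the adjusted phase difference and its 95% CI as the reported result. For 10-CS, state that its own ED-interview score is the cognitive covariate.

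State when the ED-interview scales are taken relative to the offer of the cart. Because in the post phase they may follow it, report EQ-5D, GDS-15 and 10-CS both with and without the ED-interview value. The three function scales can be adjusted directly; that they would not shift within an ED stay is a judgement, not something the document states.

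The cost is two or three sentences and no new data, staff or patients. The downside is that any cart effect already present at the ED interview is partly removed by the adjustment, which is why the paired presentation is needed. The text should be settled before recruitment opens in April 2026.

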#### Exclusion criteria.

Decline to participate in the study or use the comfort menu and cart.Absence of a companion able to consent to study participation and provide necessary information for patients with altered mental status or cognitive impairment.Decreased level of consciousness.Hemodynamic instability.Acute respiratory failure.Inability to be contacted by phone for the follow-up interview.

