#### Initial interview.

The interview will start with a questionnaire adapted from Lichen et al. (2021) and McCusker et al. (2018) [2,3].

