**Table pone.0332773.t001:** 

Questions adapted from Lichen et al. (2021)			
* Question *		* Response options *	
*During your stay in the ED, what was your average comfort level?*		Very comfortable; Comfortable; Somewhat comfortable; Somewhat uncomfortable; Uncomfortable; Very uncomfortable	
*As a person in the emergency department, do you feel you were offered care specific to your individual needs (I.e. needs related to communication, hearing, vision, etc.)?*		Strongly agree; Somewhat agree; Neither agree nor disagree; Somewhat disagree; Strongly disagree	
Additional questions in the post-implementation phase			
*Did you use any of the items or services offered in the Geriatric Cart?*		Yes; No	
*Knowing that these items or services were available, even if I did not use them, made me feel more comfortable*		Strongly agree; Somewhat agree; Neither agree nor disagree; Somewhat disagree; Strongly disagree	
*The items I requested from the comfort cart made me feel more comfortable during my visit today*		Strongly agree; Somewhat agree; Neither agree nor disagree; Somewhat disagree; Strongly disagree	
*Having the comfort cart available improved my overall experience today*		Strongly agree; Somewhat agree; Neither agree nor disagree; Somewhat disagree; Strongly disagree	
*Having the comfort cart gave me more independence during my visit today*		Strongly agree; Somewhat agree; Neither agree nor disagree; Somewhat disagree; Strongly disagree	

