#### Follow-up interview.

A second research assistant, blinded to the initial assessment and ED care details, will conduct a phone interview 30 days (± 2 days) post-initial assessment. This interview will assess the following:

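### The blanket mixed-model rule for missing data does nothing for outcomes measured once per patient, including the primary questionnaire, or for missing adjustment covariates

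*Protocol article*

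**What the plan says.** The Data management and statistical analysis section of the protocol article has one sentence on the subject: "Missing data will be handled though mixed effects model". It names no outcome, no level of clustering and no exception. The comparisons listed just before it (t-test, ANOVA, Wilcoxon, Kruskal-Wallis, chi-square, Fisher) all work on observed values. The same paragraph promises adjustment for confounders and gives baseline frailty, cognitive impairment and clinical severity as examples.

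That section also fixes the primary outcome instrument: "For the primary objective evaluating the impact of the comfort menu and cart on the experience of older patients we will use the questionnaire". It is given at the first contact ("The interview will start with a questionnaire adapted from" two published sources), and its leading item asks for one summary of the whole stay: "During your stay in the ED, what was your average comfort level". It is not among the items of the follow-up interview. The two phases contain different patients: "132 patients will be required in each group (pre- and post-intervention), totaling 264 participants".

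There is one later contact, when a second assistant "will conduct a phone interview 30 days (± 2 days) post-initial assessment". Its table includes counts such as "Number of ED visits since the initial visit". Length of stay and costs come from the medical record and administrative databases. The exclusion list ends with "Inability to be contacted by phone for the follow-up interview" and does not say when this is judged.

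**The concern.** The sentence reads as though missing data are taken care of throughout. That is true only where a patient has a second measurement of the same outcome for the model to draw on. Where there is one value per patient and it is missing, the patient contributes nothing, and the analysis is of complete cases whatever the model is called. A mixed model also does not fill in a missing covariate.

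Two things are at stake. Adjusted analyses, including the primary one, would lose patients who lack a covariate. The inclusion criteria admit patients for whom a companion answers, and a performance test such as the 10-CS may well be missing for them, so the loss would probably fall on the cognitively impaired. Single outcomes collected by telephone would be analysed only in those reached at day 30, with no stated check on whether loss is related to outcome.

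**Working it through.** **1. Count the measurements per patient** (initial-interview, baseline-data and follow-up tables; chart-review section).

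| Outcome | In the ED | Day 30 | Same measure twice? | Exposed to telephone loss? |
|---|---|---|---|---|
| Patient experience (primary) | yes | no | no | no |
| ED readmissions | no | yes | no | yes |
| Falls | past-year history only | falls since the visit | no | yes |
| Delirium | DTS/bCAM | FAM-CAM | no, different tools | yes |
| Mortality | no | yes | no | yes |
| Mood (GDS-15) | yes | yes | yes | yes |
| Quality of life (EQ-5D) | yes | yes | yes | yes |
| Function (Katz, Barthel, Lawton) | yes | yes | yes | yes |
| Cognition (10-CS) | yes | yes | yes | yes |
| Length of stay, costs | records | records | no | no |

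The follow-up table has eight domains: four repeated from baseline and four single. By instrument, six of ten are repeated. Staff experience is a further outcome with no repeat schedule stated.

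**2. What the model does with one row per patient.** Write y_i = β0 + β1·phase_i + β2·x_i + b_i + e_i, with b_i the patient effect.

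- Var(y_i) = σ_b² + σ_e². Only the sum can be estimated.
- If y_i is missing, the patient's likelihood contribution is the integral of the density over y_i, which is 1. The patient carries no information on β1.
- If x_i is missing, a model conditional on x_i cannot use the patient at all.

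**3. Numerical check.** In a simulated data set of 264 patients (132 per phase) with 211 outcomes observed:

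| Model | Patients used | Phase effect | Reported SE |
|---|---|---|---|
| Least squares, complete cases | 211 | 0.4348 | 0.133 |
| Random patient intercept | 211 | 0.4348 | 0.095 |

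The mixed model used the same patients and gave the same estimate. It split the residual variance of 0.907 into two equal parts of 0.453, an arbitrary division. The fit warned that the Hessian was not positive definite, so its smaller SE cannot be trusted.

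**4. Where the rule does work.** In 400 simulated trials of 132 per phase (true difference 0.50; in one phase, loss of the day-30 value depended on the baseline value; about 21% missing in the run displayed), unadjusted complete cases gave 0.65. A likelihood using both occasions gave 0.50. All settings were assumed. The correction came from a baseline value of the same outcome, which the single outcomes do not have. The gap of 0.65 − 0.50 = 0.15 is therefore not an estimate of bias in this trial.

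**5. Size of the exposure.** The article gives no expected loss at day 30, so a range is assumed.

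- 15%: 0.15 × 132 = 19.8, about 20 per phase, leaving about 112.
- 20%: 0.20 × 132 = 26.4, about 26 per phase, leaving about 106.

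These figures apply to the four single outcomes collected by telephone. They do not apply to the primary outcome, length of stay or costs.

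**The case against.** **The detail may sit in the SAP.** Outcome-by-outcome methods commonly do, and their absence is no finding. But the article states a rule, without limits, that cannot do what it claims for the primary outcome. That is a rule stated wrongly.

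**Complete-case analysis need not be biased.** This stands. If only the outcome is missing and loss depends only on phase and the adjusted covariates, the adjusted complete-case estimate is valid. Imputing the outcome from much the same covariates then adds little. Nor does imputation under missing-at-random cure loss that depends on the outcome itself, so the fix needs a sensitivity analysis as well.

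**The questionnaire has several items.** A model with items nested in patients could use partly completed questionnaires, and a staff-level effect could serve repeated staff interviews. The article specifies neither, and neither recovers a wholly missing primary response.

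**Stronger readings that the documents do not support.**

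- A reader might infer that the primary result is seriously threatened. The questionnaire opens a face-to-face interview after consent, with direct electronic entry, so few answers should be missing.
- A reader might infer that most day-30 outcomes are unprotected. Half of the domains are repeated from baseline, and the rule suits them.
- A reader might infer that the telephone criterion removes patients at day 30 after their primary outcome has been observed. It stands in an eligibility list whose clinical items are judged at enrolment, and the follow-up table provides for recording date and cause of death. Only the timing of the criterion is unstated.
- A reader might add GDS-15 to the missing covariates. It is not among the adjusters that the article names.

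**Conclusion.** The concern holds in a limited form. For the primary questionnaire and for ED readmissions, falls, FAM-CAM delirium and mortality, the stated rule is equivalent to complete-case analysis when the value is missing. In any adjusted analysis it also drops patients with a missing covariate. For mood, quality of life, function and cognition it is a reasonable choice under missing-at-random.

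The practical weight lies in the covariates and the four single telephone outcomes: about 20-26 of 132 patients per phase if 15-20% are lost, a range that is assumed. The number of missing covariates cannot be derived from the article. No direction or size of bias is established. The correction should be made because the plan claims a protection that its design does not provide, not because the primary conclusion is shown to be unsafe.

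**What to change.** Replace the sentence with a rule by type of variable:

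1. Use a mixed model only for scales taken at baseline and day 30 (GDS-15, EQ-5D, Katz, Barthel, Lawton, 10-CS).
2. Multiply impute missing adjustment covariates and partly missing questionnaire items, using phase, age, frailty, Charlson index, NEWS2 and respondent type.
3. Analyse single day-30 outcomes with covariate adjustment or imputation, plus a sensitivity analysis in which loss depends on the outcome.
4. Complete reattendance at the study site and in-hospital death from hospital records, which are already being opened for length of stay and costs. Records cannot supply visits to other hospitals, so report site reattendance separately from the telephone count.
5. Do not impute quality of life or function after death; report deaths as deaths.
6. State that every patient with an ED interview enters the primary analysis, and word the telephone criterion as assessed at enrolment.

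The cost is a few sentences, one reworded criterion, two more fields from records and a little more analysis work. Multiple imputation is available in the software already named. The sample size and visit schedule do not change, and the wording can be settled before recruitment opens in April 2026.
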